## Abstract

We developed a physical exercise (PE) program for people with Intellectual and Developmental Disabilities (IDD), aiming to determine the effects on physical fitness, health, cognitive ability, and quality of life (QoL). Using experimental methodology, this intervention study recruited 21 adults (18 to 65 years old), institutionalized and with no other associated pathology, who will be allocated to one of the different groups: (i) gym/indoor intervention group (using weight machines), (ii) outdoor intervention group (using low-cost materials), or (iii) control group (without specific intervention, who continue with their normal daily activities). Both intervention groups will engage in 45 min of training per session, twice a week, for 24 weeks. Assessments will be conducted at baseline (initial assessment), 3 months (mid-term assessment), and 6 months (final assessment). Variables assessed include anthropometrics, body composition, functional capacity, muscle strength, general health, cognitive ability, and QoL. The results of this study will assist in the development of more effective strategies, recommendations, and interventions to ensure better and greater adherence to PE by institutionalized individuals with IDD, namely, recommendations for assessment, prescription, and implementation of PE for this population. Additionally, we intend to make available two PE programs, if they are adapted and promote positive effects.

## 1. Introduction

Individuals with Intellectual and Developmental Disabilities (IDD) (new designation according to *ICD-11 International Classification of Diseases 11th Revision*) [1] are characterized by a deficit of intellectual and adaptive functioning in the conceptual, social, and practical domains. This individual can be identified with mild, moderate, severe, and profound degrees and are a type of disability that develops before age 22 [2,3].

In this population, several studies show improvements in physical fitness through the implementation of physical exercise (PE) programs, increasing the success in performing activities of daily living [4,5]. Performed in a regular way, PE is also associated with brain development, particularly the frontal and temporal region, due to the cortical activity it stimulates [6], affecting brain plasticity and improving cognitive ability [7,8]. In individuals with IDD, a simple 20 min treadmill walking training provides significant improvements in choice response time and processing speed, attention, and inhibition [9,10]. In the same sense, the improvements found are not only in terms of physical fitness and cognitive ability variables, but also in quality of life (QoL) [11]. The QoL of this population is a construct consisting of a set of factors that determine their well-being, or their perception of their social position, including individual needs, experiences, and sociocultural values and preferences [12,13]. In the Pérez-Cruzado and Cuesta-Vargas [14] study, an 8-week PE intervention program promoted physical fitness and QoL in 40 individuals. In addition, a previous study with a sample of 529 individuals with IDD, despite being an intervention with physical activity, identifies benefits in each of the domains of the aforementioned model [15].

Despite the importance of PA and/or PE benefits, this population has high rates of sedentarism and low levels of physical activity engagement [16,17], not meeting the recommendations [18,19], which puts them at greater risk of developing chronic diseases [20] and consequent premature death [21,22]. The risks of physical inactivity in people with disabilities increase when compared to the general population: higher prevalence of hypertension (25 to 41% compared to 29% in the general population); obesity (30.8 to 36.6% compared to 18.2 to 18.5%); and metabolic syndrome (21 to 29.3% compared to 13.5% to 17.9%) [23,24]. In addition, as the degree of disability increases, physical activity levels decrease more significantly [25], affecting their physical fitness, capacity to perform activities of daily living, and independence [26]. To promote their life conditions, people with IDD should be integrated into PA and PE practice, according to recent recommendations [18,19].

One of the possible reasons for these low levels of practice is the existence of barriers that hinder their practice. Among them, we can find factors such as financial cost and lack of adapted PE [27,28]. To reduce the impact of these barriers, it is important to develop PEs. Besides being adapted to the individuals, they must be accessible to any type of context and financial availability, both for the individuals and the support institutions. In addition, the development of these PE may contribute to the reduction in the risk of the onset of metabolic and cardiovascular diseases, which decreases healthcare costs and promotes physical fitness, functionality, and QoL. Therefore, the main objective of the present study is to evaluate and compare the effectiveness of two different 24-week PE programs on levels of physical fitness, general health, dementia/cognitive decline, and QoL in individuals with IDD.

Therefore, the following hypotheses will be operationalized: (i) individual with IDD increased physical fitness after 12 and/or 24 weeks of PE; (ii) individual with IDD increased general health after 12 and/or 24 weeks of PE; (iii) individual with IDD increased dementia/cognitive decline after 12 and/or 24 weeks of PE; (iv) individual with IDD increased QoL decline after 12 and/or 24 weeks of PE; (v) there was a difference between groups on levels of physical fitness after 12 and/or 24 weeks of PE; (vi) there was a difference between groups on levels of general health after 12 and/or 24 weeks of PE; (vii) there was a difference between groups on levels of dementia/cognitive decline after 12 and/or 24 weeks of PE; and (viii) there was a difference between groups on levels of QoL after 12 and/or 24 weeks of PE.

## 2. Materials and Methods

### 2.1. Study Design

The present study protocol describes a non-randomized experimental study, consisting of three groups (1:1 allocation), to assess and compare the effectiveness of two different combined PE (strength + aerobic capacity) for individuals with IDD.

Participants will be allocated to one of the three groups: (i) indoor training group (IG) with sessions carried out in a gym, using weight machines; (ii) outdoor training group (OG) with sessions using low-cost materials; and (iii) control group (CG) with participants continuing to do their normal activities (participation in one of the exercise interventions will not be allowed), based on their interests and availability to be involved with PE programs.

Participants from both intervention groups will participate twice a week, in a 24-week supervised PE program, with sessions lasting 45 min per session. All outcome measures will be collected at three different time moments, at baseline (time 0, baseline assessment, or week 0), at mid-term (time 1, intermidiate assessment, week 12), and at the end of the intervention program time 2, final assessment, week 24). The measurements will be performed after 48 h, after the last workout in both groups, and always in the morning. Figure 1 shows the participant flow for this trial.

### 2.2. Participants

Adult volunteers, institutionalized in a support institution, located in Leiria, Portugal, recruited by the non-probabilistic convenience method will participate in the program.

In the first step, an individual explanation will be held about the procedures and objectives of the study, as well as the potential benefits, risks, and the time needed for the development of the project.

In a second moment, the participants/family members/tutors will sign a free consent form. Inclusion criteria will be defined: (1) adults with IDD, diagnosed with mild, moderate, or severe IDD; (2) age over 18 years) success in performing movements such as pulling/pushing; (3) capacity to perform the assessments. Exclusion criteria will be defined: (1) individuals who cannot commit themselves for 6 months; (2) individuals with other associated pathologies; (3) contraindications to PE (e.g., high blood pressure); (4) inability to walk unaided; (5) profound IDD; (6) inability to communicate; (7) non-delivery of signed informed consent.

Due to the characteristics of this special population and logistical constraints intrinsic to the development of intervention studies, the sample will consist of the first 21 individuals who agree to participate in the program, aged between 18 and 65. After that, participants will be allocated to one of the three groups. A power analysis (calculated using *G*Power*, version 3.1.9.7 [29] showed that a sample of at least 15 was required to detect a medium effect size (*ES*) of 0.5 (*α* = 0.05, 1 − *β* = 0.95) using a repeated-measures analysis of variance (*ANOVA*), in agreement with some previous studies [30,31]. The effect size of 0.5 was chosen given that this value was verified from studies investigated the effects of exercise on the variables of interest in our study [32,33,34].

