## 8. Statistical Analysis

In the statistical analysis, descriptive parameters will be used (mean ± standard deviation or percentage) normality and homogeneity will be verified through the *Shapiro*–*Wilk* test and the *Levene* tests, respectively. The existence of significant differences between groups will be analyzed using the *Kruskal*–*Wallis* test and between times using *Wilcoxon* or *Friedman* test. The non-parametric statistic was defined according to the “Central Limit Theorem” [63], in the sense that it will require 30 participants in the sample to have a normal distribution. The magnitudes of the differences will be examined using the *Cohen’s d* effect size [64]. Likewise, associations across studies variables will be verified through the *Spearman* coefficient of bivariate correlations (*r* = 0.10 to 0.29—small; *r* = 0.30 to 0.49—moderate; *r* = 0.50 to 1—strong) [65]. The significance level adopted for all analyses will be *p* < 0.05. For data processing, the computer program *Statistical Package for Social Sciences* (SPSS Science, Chicago, IL, USA), version 28 will be used.

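### The sample size of 15 for 95% power fits a within-subject ANOVA effect with 0.5 read as Cohen's f, which is large rather than medium, and does not cover the planned Kruskal-Wallis group comparison

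*Protocol article*

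**What the plan says.** All references are to the protocol article.

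- **Sizing (Section 2.2).** The G*Power calculation "showed that a sample of at least 15 was required to detect a medium effect size". The inputs are given as "to detect a medium effect size (*ES*) of 0.5 (*α* = 0.05, 1 − *β* = 0.95"), and the model as "using a repeated-measures analysis of variance (*ANOVA*), in agreement with some previous studies". The effect-size metric, the effect tested (time, group or interaction) and the correlation among repeated measures are not stated.
- **Enrolment (Section 2.2).** For logistical reasons, "the sample will consist of the first 21 individuals who agree to participate in the program".
- **Design (Section 2.1).** The study is described as "consisting of three groups (1:1 allocation"), and "All outcome measures will be collected at three different time moments". At 21 participants this gives 7 per group.
- **Objective (Section 1).** The aim is to "evaluate and compare the effectiveness of two different 24-week PE programs". Hypotheses (v) to (viii) each concern a difference between groups in levels after 12 and/or 24 weeks.
- **Analysis (Section 8).** Groups are compared by Kruskal-Wallis, and times by Wilcoxon or Friedman. The choice is made in advance: "The non-parametric statistic was defined according to the" central limit theorem, with 30 participants as the threshold. Cohen's d is the only effect-size metric named in the article.
- **Exclusions (Section 7).** Participants attending fewer than 75% of sessions are left out of the analysis.

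**The concern.** Two things do not fit together.

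First, the label and the number. G*Power's repeated-measures ANOVA takes Cohen's f, for which the usual conventions are 0.10 small, 0.25 medium and 0.40 large. A value of 0.5 is medium on the d scale and more than large on the f scale. A sample as small as 15 suggests that 0.5 went in as f.

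Second, the sized test is not a planned test. Section 8 has no repeated-measures ANOVA, and none of its three tests assesses a group-by-time interaction. The comparison of groups, which the objective and half the hypotheses concern, has no power statement of its own.

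At stake is how a null group comparison would be read. Set beside a claim of 95% power for a medium effect, it could be taken as evidence that the programmes do not differ from each other or from usual activity, when the planned test may have had little chance of showing a difference.

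**Working it through.** **Inputs from the article:** k = 3 groups, m = 3 times, alpha = 0.05, power 0.95, effect size 0.5, stated minimum N = 15, planned N = 21. **Assumptions:** correlation rho = 0.5 (varied), sphericity, equal groups.

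**Formulas (noncentral F, as in G*Power):**
- Time: lambda = f²·N·m/(1 − rho), df = m − 1 and (N − k)(m − 1).
- Interaction: same lambda, df = (k − 1)(m − 1) and (N − k)(m − 1).
- Between groups: lambda = f²·N·m/(1 + (m − 1)·rho), df = k − 1 and N − k.

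**Step 1. Reproduce 15, reading 0.5 as f.**
- Time, N = 15, rho = 0.5: lambda = 0.25 × 15 × 3/0.5 = 22.5, df 2 and 24, power 98.4%. At N = 12, lambda = 18 and power is 94.6%. In multiples of three, the answer is 15.
- Interaction, N = 15, rho = 0.5: lambda = 22.5, df 4 and 24, power 94.8%, just short of target. At rho = 0.6, lambda = 28.1 and power is 98.2%; N = 12 gives 93.3%, so the answer is again 15.
- Between groups, N = 15, rho = 0.5: lambda = 0.25 × 15 × 3/2 = 5.625, power 44.9%. It needs 45, and has 63.1% at N = 21.

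So 15 fits a within-subject effect at f = 0.5. The article does not say which one.

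**Step 2. Read 0.5 as a medium effect.** For two equal groups f = d/2, so d = 0.5 gives f = 0.25. Total N for 95% power at f = 0.25:

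| Effect | rho 0.3 | rho 0.5 | rho 0.8 |
|---|---|---|---|
| Time | 60 | 45 | 21 |
| Interaction | 72 | 54 | 24 |
| Between groups | 135 | 168 | 219 |

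At N = 15 and rho = 0.5 the time effect has lambda = 0.0625 × 15 × 3/0.5 = 5.625 and power 50%. To recover lambda = 22.5 at N = 15 with f = 0.25, one needs 1 − rho = 0.0625 × 45/22.5 = 0.125, that is rho = 0.875. Nothing in the article states so high a correlation.

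**Step 3. Power of the planned group test.** Kruskal-Wallis simulated with normal data of SD 1, equally spaced means (−a, 0, a) with a = f·√1.5, the chi-square critical value, and scores at one time point:

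| Per group | f = 0.25 | f = 0.5 |
|---|---|---|
| 7 | 13% | 41% |
| 5 (for example after attendance exclusions) | about 9.5% | 28% |

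**Step 4. Change scores instead.** With the same group differences on the raw-score scale and 7 per group, the SD of a change is √(2(1 − rho)):

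| rho | f = 0.25 | f = 0.5 |
|---|---|---|
| 0.5 | 13% | 41% |
| 0.7 | 19% | 63% |
| 0.8 | 27% | 81% |
| 0.9 | 50% | 98% |

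Power stays below 95% up to rho = 0.8. It passes 95% only for the large effect at a correlation near 0.9.

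**The case against.** Much can be said for the authors, and three stronger readings should be resisted.

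**That 15 holds only for a time effect pooled over all groups.** A reader might infer this from the exact match in Step 1. The article does not support it, because the interaction comes to 94.8% at rho = 0.5 and returns exactly 15 at rho = 0.6. Neither the effect nor the correlation is stated.

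**That no between-group hypothesis has 95% power under any analysis.** This also goes too far. A group-by-time interaction asks whether groups change differently, and at f = 0.5 and N = 21 its ANOVA power is 96% (rho 0.3) to over 99% (rho 0.5 and 0.6). A Kruskal-Wallis test on change scores would also have about 99.5% power for an interaction of that size at rho = 0.5. But in a linear pattern such an interaction puts the extreme groups' changes 3 SD apart, which is far from medium, and Section 8 plans no interaction test.

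**That per-group signed-rank tests can never reach significance.** The smallest exact two-sided p is 2/2⁵ = 0.0625 with 5 per group, but 2/2⁷ = 0.016 with the planned 7. The problem would arise only if losses brought a group to 5.

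Two further caveats stand. The conversion f = d/2 is for two groups; with three equally spaced means and extremes 0.5 SD apart, f is 0.5/√6 = 0.204 and Kruskal-Wallis power is about 10%. Section 8 also does not say whether levels or changes are compared, although hypotheses (v) to (viii) speak of levels.

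Finally, enrolment of 21 was set by logistics, and Section 9 already calls the work a pilot study. That limits the consequences but does not make the stated power correct.

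**Conclusion.** The concern holds in a limited form. The figure of 15 for 95% power fits a within-subject ANOVA effect with f = 0.5, which is not medium. With f = 0.25 it does not reproduce at any correlation examined from 0.3 to 0.8; the time effect needs 21 to 60 and the interaction 24 to 72.

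The 95% does not carry over to the group comparison that Section 8 plans. With 7 per group, normal data and scores at one time point, power is about 13% at f = 0.25 and 41% at f = 0.5. It is higher on change scores when the correlation exceeds 0.5 (27% to 81% at 0.8), and lower after attendance exclusions. The ANOVA figures assume sphericity. Correlations are assumed throughout, because the article gives none.

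**What to change.** Keep 21 participants and rewrite the power paragraph in Section 2.2 so that it:

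- names the effect-size metric, the effect sized (time or interaction) and the correlation that were entered in G*Power;
- drops the word medium if 0.5 was f, or recalculates if 0.5 was d, giving the correlation beside any resulting number;
- does not present 95% power as covering the comparison of groups;
- states power for Kruskal-Wallis with 7 per group, with its assumptions, including whether scores at one time or changes are compared;
- labels group differences as pilot estimates, to be reported with 95% confidence intervals.

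The cost is one reworded paragraph, a matching sentence in Section 8, and a less favourable stated power. No extra participants are needed.

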### 2.3. Informed Consent

A comprehensive explanation of the study (material and methods inclusive) by the research leader and the host institution will be conducted to allow participants/family members/tutors to be fully informed. The subject group will be given adequate time to decide on their participation; however, the first 21 individuals who agree to participate in the study will be part of the sample. To do this, participants/family members/tutors must sign and deliver the informed consent form.

### 2.4. Protocols

The development of 2 training programs, one Indoor (Table 1) and one Outdoor (Table 2), occurred taking into account one of the barriers identified by individuals with ID and their caregivers and/or family members/tutors to physical inactivity: lack of adapted PE and the financial cost of the practice [27].

The indoor training program should be performed in the context of a gym/health club/association, using the available materials. The outdoor training program should be performed with low-cost materials, allowing its application in any economic context. The use of some low-cost equipment is suggested, such as elastic bands and shin guards of different weights. However, if this is not possible, the outdoor PE can be performed with bodyweight only or with water/sand bottles. These programs were as close as possible to the recommendations suggested by [18], as well as to the scientific evidence [4].

Strength training was combined with aerobic training in the same session, performed twice a week, for 45 min, always at the same time, namely, in the morning. Each training session was divided into 4 phases (warm-up, cardio, resistance, and flexibility training). Considering the initial assessment and physical fitness of each participant, the intensity is progressive throughout the program, and the stimulus and load will be continuously adjusted in order to promote the consequent adaptation processes in the body, taking into account the principle of progressive overload. Although a set of exercises are suggested, the planning is not fixed and may be adjusted to the characteristics of individuals. First, the required movement will be practiced without any kind of material. All participants will have familiarization sessions with the training materials, prescribed movements, and with the space and with all the routines that an exercise session involves. Occasionally, if individuals mention/evidence any kind of mental/psychological or physical problem, the training intensity is adjusted to allow participation in the exercise session.

The programs will be supervised by two PE technicians, trained in a standardized manner, with recovery periods of at least 48 h. The control of training intensity will be carried out using heart rate monitors (Polar M400, Kempele, Finland), through the formula used to calculate the Maximum Heart Rate [35] and also the equation for individuals with Down Syndrome [18] to calculate the target heart rates. If any subject exceeds the target intensity, they will be instructed to decrease or even rest.

#### 2.4.1. Indoor Training Program

The indoor PE program was carried out in a gym with weight machines. Seven heart rate monitors and seven gym towels will be required. The PE program was divided into four parts. Part I: playful game or shuttle run (5 to 7 min). Part II: aerobic training; Part III: strength training; Part IV: 4 static stretches/cool down. Table 1 shows the training program in detail.

#### 2.4.2. Outdoor Training Program

The program will be conducted in an outdoor space with elements of nature, where resistance elastic bands and shin guards for the ankles will be needed. The outdoor PE program was carried out in a natural environment near the institution. Natural environments, which, for this experimental study, are defined as “any outdoor spaces with elements of nature, from pure or semi-natural areas to urban green or blue spaces, including green infrastructure” [36]. The PE program was divided into four parts. Part I: playful or shuttle run; Part II: aerobic training; Part III: strength training; Part IV: 4 static stretches/cool down. Progression of exercises with changing the resistance of the TheraBand’s and shin guards. Table 2 shows the Outdoor PE program in detail.

#### 2.4.3. Control Group

Subjects in the control group will be encouraged to keep their usual lifestyle and their attendance at exercise sessions corresponding to the two exercise programs will not be allowed.

### 2.5. Assignment of Intervention and Blindness

After obtaining informed consent and finishing the initial assessments, the volunteers will be distributed to the three groups, according to their intention to participate in the study. Due to the nature of the intervention, after the initial assessment, it will not be possible to randomize the sample by groups, nor will it be possible to “blind” the participants and lead investigator belonging to the group. Upon delivery of the informed consent, a code will be assigned to each participant, ensuring the anonymity of the subjects. The researchers responsible for the evaluations will have no knowledge of which group each subject belong to, except for the principal researcher. To minimize differences in procedures, the same team will perform the assessments at different moments.

